### Sex differences influence genetic risk for AD

1.6

Beyond modifiable risk factors for AD, sex appears to interact with a known genetic risk factor (Ungar et al., 2014; Holland et al., 2013; Altmann et al., 2014; Damoiseaux et al., 2012) for AD that can be assessed well before aging occurs: the *ε4* form of the Apolipoprotein E (*ApoE*) gene (Alzheimer's disease facts and figures, 2024). Relative to *ApoE*-ε4 carrying males, *ApoE*-ε4 carrying females have higher risk of earlier AD onset (Payami et al., 1994; Farrer et al., 1997; Aggarwal and Mielke, 2023), worse cognitive outcomes and performance (Aggarwal and Mielke, 2023; Raber et al., 1998; Arenaza-Urquijo et al., 2024; Leung et al., 2012; Andrews-Zwilling et al., 2010), even earlier in life (Reynolds et al., 2019), and appear to have brain health (Aggarwal and Mielke, 2023; Sampedro et al., 2015) and pathology (Cacciottolo et al., 2016; Hohman et al., 2018; Shokouhi et al., 2020) impacted differently. Interestingly, both inflammation and the microbiome are associated with *ApoE* alleles. Specifically, the *ε4* high risk variant has been associated with altered microbiome composition and increased neuroinflammation in both mice and humans (Kloske and Wilcock, 2020; Tai et al., 2017; Tzioras et al., 2019; Tran et al., 2019; Zajac et al., 2022). Several recent studies in both mice and humans have also demonstrated that sex and *ApoE-ε4* interact to affect the microbiome and inflammation (Duarte-Guterman et al., 2020; Seo et al., 2023; Maldonado Weng et al., 2019; Ayton et al., 2021). Together, these data suggest that a mechanistic understanding of sex differences in AD risk will emerge only when examining *ApoE-ε4*, the microbiome, and inflammation together in the context of educational opportunities.

### Towards a comprehensive understanding of sex-related AD risk

1.7

The research reviewed so far highlights that female sex might be related to higher AD incidence by virtue of its interactions with several known risk and resilience factors for AD – genetic variation, education and upwards mobility – and that some of these impacts may be realized, especially earlier in life, via functioning across the brain-gut axis. As such, an understanding of sex-related risk for AD will only emerge with a comprehensive analysis that includes all of these variables assessed in development, before AD pathology and cognitive decline is evident. Given that the majority of these prior findings are based on observational study designs, causal designs where protective and risk factors are experimentally manipulated are invaluable. The Reducing Inequities through Social and Educational Change Follow-Up in Early Adulthood Extension study (RISE-Up EA+; R01AG089426) will address these issues by providing a unique developmental and experimental framework for understanding the impacts of sex on AD risk, especially via pathways that interact with striving-related stress and may set the stage for brain-gut axis changes which foreshadow later emerging cognitive and brain-pathology.

The RISE-Up EA+ study leverages a natural quasi-experimental cohort that began in 2013 (RISE-Up) to understand the impact of educational experience on youth health outcomes and substance use (R01DA033362). The random admissions lottery of five high-performing charter schools in Los Angeles was initially used to find two comparable groups of adolescents that were exposed to high-and lower-performing public high schools. These groups had similar baseline demographics, prior academic performance, family characteristics, and neighborhood exposures, and have been followed longitudinally during adolescence from ages 13 through 18 (phase 1: RISE-Up-HS; R01DA033362), during their transition to emerging adulthood from ages 18 through 24 (phase 2: RISE-Up-T2A; R01DA033362), and into early adulthood from ages 24 through 28 (RISE-Up EA; R01A082868) while collecting various self-reported health metrics to understand the impact of education on health outcomes (see Fig. 1 for a timeline of study phases). (Wong et al., 2014, 2022) To assess cognitive ability and brain health, as well as associated inflammatory and microbiome-related biology, we will conduct an add on to the RISE-Up EA study (called RISE-Up EA+) to collect additional cognitive and neurobiological measures after participants began enrollment in RISE-Up EA when the cohort is aged between 24 and 26 years. Findings from earlier timepoints in the RISE-Up study position it to address the unique question of how sex-related AD risk may manifest across the lifespan. Specifically, earlier waves from grade 9 through grade 11 (RISE-Up-HS) identified that adolescents attending high-performing schools were less likely than those in lower-performing schools to engage in risky substance use and have substance using peers in their social network (Dudovitz et al., 2018). Recent results also show that young adults aged 20 and 21 (RISE-Up-T2A) that attended high-performing schools had lower rates of hazardous or dependent alcohol use, had lower cannabis misuse scores, less delinquent behaviors, and higher rates of fair/poor mental health scores (Wong et al., 2022). Differences in physical health outcomes were found between males and females, where rates of fair/poor physical health and overweight/obesity were lower for young adult males that attended high-performing schools but higher rates were found for young adult females (Wong et al., 2022). Controlling for academic outcomes (e.g., high school graduation and grade point average, standardized test scores and college matriculation) had no impact. This may indicate that the developmental pathways for later AD risk may already be in motion for females with greater mobility opportunity in the RISE-Up study (Wong et al., 2022). However, the precise biological mechanisms informing this risk are still unclear. In this paper, we will summarize the study aims, hypotheses, and protocol for the RISE-Up EA+ Study that aims to understand how factors contributing to health after mobility opportunity impact sex-related risk for developing AD later in life.

**Fig. 1 fig1:**
[figure not shown]
*Timeline of RISE-Up Study Phases*. 1270 participants were recruited and enrolled at baseline in the RISE-Up High School Study and were followed throughout grades 9-12. 977 participants continued with the RISE-Up Transition to Adulthood Study and were followed through age 24. The RISE-Up into Early Adulthood Study phase is ongoing with the goal of recruiting 750 participants ages 24-28 that previously participated in the baseline study. The RISE-Up Early Adulthood Extension Study is ongoing with the goal of recruiting 300 participants ages 24-26 from the RISE-Up EA Study. Created in https://BioRender.com.

## Study aims & hypotheses

2

In the RISE-Up EA+ Study, we will collect measures of striving-associated stress through self-report. We will quantify health risks by indexing brain-gut axis function via inflammatory markers in blood, the microbiome metagenome in stool, *ApoE* gene allele via buccal swab, brain health through Magnetic Resonance Imaging (MRI), and general cognitive ability through standardized neurocognitive tests. Using these measures, we will examine how sex moderates the links between youths afforded mobility opportunity by randomization into high performance schools vs. those who were not (i.e., waitlisted) and brain health, general cognitive ability, inflammatory markers, and the microbiome (see Fig. 2 for the conceptual model). Both sex assigned at birth and gender identity might contribute to potential differences observed in this study and we will aim to try to parse these constructs when we can, highlighting that sex-related differences may be, in part, due to stress related to gender roles and expectations. The aims of our study are as follows:1.**Identify the impact of mobility opportunity on young adult general cognitive ability (GCA) and brain health (which we propose will link with later life resilience to AD), and determine if those associations are moderated by sex.** We hypothesize (H1) that mobility opportunity will be associated with worse brain health in females, but better brain health in males, relative to static opportunity. Second, we hypothesize (H1.2) that mobility opportunity will be associated with greater GCA in both males and females, relative to static opportunity.2.**Establish links between mobility opportunity, inflammatory markers, and microbiome enrichment for inflammatory genes and pathways, and determine whether those links are moderated by sex and sex-related vulnerabilities (adolescent stress).** We expect (H2) that relative to static opportunity, mobility opportunity in females (but not males) will have a greater average expression of inflammatory genes in blood, and genes and pathways involved in inflammation in stool.

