
### Sex as a moderator of the impacts of education on risk for AD

1.3

Notably, while education and higher SES are well-established protective factors for AD, such associations may be complicated when considered in the context of sex. Importantly, two older studies both found that women with fewer years of education were at higher risk for AD compared to women with more years of formal education, an association that was absent in men (Letenneur et al., 2000; Launer et al., 1999). These results, though preliminary, suggest that the buffering effects of education on AD risk may be differentially expressed as a function of sex, and particularly important for women. However, there is a dearth of research testing this hypothesis formally (Liu et al., 2022), underscoring the need for more work in this space. At the same time, recent findings from a randomized education intervention study in majority low-SES youth show that while both females and males in the intervention group (i.e., lottery winners assigned to attend a high-performing school) were both more stressed regarding school performance and school/leisure balance compared to the control group (i.e., waitlisted youth), females in the intervention group experienced increased self-reported perceived stress (i.e., subjective current stress in life more broadly) while striving for higher education during adolescence and early adulthood (Wong et al., 2026). However, this was not true for striving males as less perceived stress was reported among males in the intervention group (Wong et al., 2026), indicating gender differences in striving-related stress responses (i.e., stress associated with higher performance education experiences). These results align with findings from the Jackson Heart Study in African American adults which show observed gender differences in stress outcomes with women reporting higher goal-striving stress compared to men in the sample (Glover et al., 2020; Cain-Shields et al., 2022b). Notably, additional observed associations from the Jackson Heart Study between goal-striving related stress and increased health risks appear to be only significant for women and not men (Cain-Shields et al., 2022a; Glover et al., 2020). Few studies have explicitly reported on sex or gender differences in striving-related psychosocial and health outcomes, but when such differences have been observed, they have generally indicated worse outcomes for females compared to males (Wong et al., 2022, 2026; De France et al., 2022). One possibility for such findings is that females striving for upward mobility may be especially vulnerable to stress due to gendered social expectations. For instance, societal expectations or norms that position women as primary caregivers can conflict with expectations in school environment/institutional demands in educational settings, creating stress. This explanation is preliminarily supported by results that show females striving for higher education (i.e., won the random lottery to attend high-performing schools) also reported significant stress at home, stress of peer pressure, and stress of financial pressure compared to females that were waitlisted to attend high-performing schools (Wong et al., 2026). This suggests that the protective effects of education against later life health outcomes and AD risk might be moderated by sex, particularly for individuals from low SES backgrounds. Additionally, given that stress has been associated with and is a risk factor for the development and progression of AD (Zhu et al., 2021; Donley et al., 2018; Lyons et al., 2022; Song et al., 2020), reducing the physiological consequences from striving-related stress may improve cognitive health trajectories later in life. Therefore, it is crucial to assess interactive factors, such as sex, and biological mediators that inform resilience and risk pathways. In particular, it is vital to understand how such stress can impact sex-associated health outcomes, such as AD, and identify factors, particularly early in life before cognitive decline or core brain pathology, including β-amyloid (Aβ) and tau pathology, are detectable, to inform prevention strategies and mitigate risk.

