Striving for better educational attainment during adolescence can be stressful for youth, seemingly more so for females, and this striving-related stress may induce consequential health problems, such as increased systemic inflammation, altered brain-gut axis signaling and other neurotoxic effects, including neuroinflammation, impacting later cognitive outcomes and AD risk. An overarching goal of this study is to critically consider and examine the potential health costs from psychosocial factors—such as stress and educational attainment—in diverse youth early in life. By pursuing this research, we may be able to assess in the future whether intervening and improving factors earlier in development, such as education and educational settings by improving and increasing support and resources while youth are striving, can ultimately impact and set the stage for health outcomes across the lifespan and later illness risk. It is critically important to note that our findings would reveal what kinds of support are needed, particularly for females early in life, to ensure such pursuits for improved future socioeconomic attainment do not evoke unintended and deleterious health consequences. In addition to increasing and maintaining cognitive reserves by improving education attainment as an important and feasible early prevention strategy for AD, prior work has also identified that reducing risk for neuropathological damage is important for slowing progression and prevention (Zhang et al., 2021). Therefore identifying early indicators and biological mechanisms of AD and related dementias is important for modulating disease development and outcomes. The presence of A β plaques and neurofibrillary tangles are both core features of the brain pathology that characterizes AD. Understanding the biological mediators, such as peripheral and central inflammation and altered gut-brain-axis signaling, that impact onset, generation and progression of these pathologies in AD is important to improve health outcomes and reduce risk.

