A strength of the RISE-Up study is its quasi-experimental design through random admissions lottery to several charter schools allowing us to sample comparable cohorts of adolescents exposed to different school environments and thus, more rigorously test the causal effect of exposure to high-performing schools on health and cognition. This design avoids the limitations of observational studies assessing health and education and allows for more control over confounding variables, such poverty, neighborhood, and family factors (Cutler and Lleras-Muney, 2006, 2010; Galama et al., 2017). One limitation of the data collected thus far in the RISE-Up cohort is its reliance on self-reported health data. The addition of objective markers of health (e.g., microbiome and inflammation) in the follow up timepoints will greatly add to the rigor of this study and expand the research scope. Furthermore, little is known about risk factors for AD that may be unfolding during young adulthood despite the knowledge that this is a pivotal period for physical and mental health. In general, more research is also needed to determine more consistent evidence for sex and gender differences in risk pathways for AD. However, the research conducted thus far highlights the urgent need to understand how and why potential modifiable risk factors modulate the risk and progression of AD, and how they can be leveraged to reduce AD risk for all. Therefore, it is critically important to assess how sex interacts with potential mechanisms that contribute to increased health risks, especially earlier in life, that may inform vulnerabilities for AD. Therefore, this study has unprecedented opportunity to identify mechanisms and explicitly assess sex-specific vulnerabilities that may in turn be used to identify optimal windows for prevention or invention efforts that optimize cognitive and physical health outcomes in youth striving for upward mobility from low socioeconomic status backgrounds.

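### Aim 2 names adolescent stress as a moderator although the article reports that the lottery changed stress; unless stress was measured before the lottery, mobility effects within stress levels cannot be read causally

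*Protocol article*

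**What the plan says.** Under Study aims & hypotheses, Aim 2 links mobility opportunity (winning the charter-school lottery rather than being waitlisted) to inflammatory markers and the microbiome, and will "determine whether those links are moderated by sex and sex-related vulnerabilities (adolescent stress". H2 and item 2 of the Fig. 2 caption mention moderation by sex only.

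Section 1.3 compares lottery winners with waitlisted youth on stress:
- General perceived stress, females: "females in the intervention group experienced increased self-reported perceived stress", described as arising "while striving for higher education during adolescence and early adulthood".
- General perceived stress, males: "less perceived stress was reported among males in the intervention group".
- School-specific stress: females and males who won "were both more stressed regarding school performance and school/leisure balance compared to the control group".

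The Discussion says that "this striving-related stress may induce consequential health problems, such as increased systemic inflammation". It presents the lottery as the reason the study can "more rigorously test the causal effect of exposure to high-performing schools on health and cognition". On timing, section 1.7 says the groups "have been followed longitudinally during adolescence from ages 13 through 18". Aim 3 lists brain health, inflammatory blood markers and the microbiome as mediators; stress is not on that list.

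**The concern.** The lottery makes winners and waitlisted youth comparable as whole groups and within levels of anything fixed beforehand, such as sex. It does not make them comparable within levels of something the lottery itself changed. A highly stressed winner and a highly stressed waitlisted participant may have reached that level for different reasons.

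The article's own account puts adolescent stress in that second class and also on the path to the Aim 2 outcome. A mobility-by-stress term, or a mobility effect within a stress stratum, could then be reported as showing that mobility is more harmful in stressed youth when it shows no such thing. A second risk arises if stress and sex share a model: the mobility-by-sex term, which is what H2 is about, would no longer measure the total sex difference.

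**Working it through.** The article gives no effect size, model or power figure for the stress moderation (its power statement concerns brain health and moderated mediation), so there is no planned figure to reproduce. The check is a comparison of statements, then an illustration with assumed values.

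**1. Is stress affected by the lottery?** Section 1.3 reports a winner-versus-waitlist difference on each type of stress it compares for both sexes. It does not name the cohort, but the design (lottery winners against waitlisted, mostly low-SES youth) matches this one.

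**2. Is stress placed on the path to the outcome?** Yes. The Discussion runs from striving to stress to systemic inflammation, and inflammation is an Aim 2 outcome.

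**3. Could the moderator predate the lottery?** The aim names neither instrument nor wave. Adolescent follow-up spans ages 13 to 18, which includes the high-school years that the lottery determined. Participants were already adolescents at baseline (median age 14.2), so a pre-lottery measure is conceivable, but none is specified. The Perceived Stress Scale in the extension covers the last month at age 24 to 26, so it is also after the lottery.

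**4. What a joint model would do.** Notation (all sizes are assumptions):
- s_F, s_M: lottery effect on stress in females and males, in SD.
- b: effect of stress on inflammation, SD per SD.
- g: effect of an unmeasured common cause on both stress and inflammation.

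The part of the mobility-by-sex difference that runs through stress is (s_F − s_M) × b. Holding stress fixed removes it. An unmeasured common cause adds a bias of −(s_F − s_M) × g².

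- Equal and opposite shifts, small: (0.2 + 0.2) × 0.2 = 0.08 SD removed.
- Equal and opposite shifts, larger: (0.4 + 0.4) × 0.3 = 0.24 SD removed.
- Same shift in both sexes: (s − s) × b = 0 removed.

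**5. Simulation check** (one million people; shifts of +0.3 in females and −0.3 in males; b = 0.4; all of the effect through stress). The true mobility-by-sex term is 0.6 × 0.4 = 0.240.

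| Quantity | No common cause | Common cause, g = 0.5 |
|---|---|---|
| Mobility-by-sex, stress left out | 0.241 | 0.244 |
| Mobility-by-sex, stress and mobility-by-stress added | 0.004 | −0.146 |
| Mobility effect in high-stress females (true total 0.120) | 0.049 | 0.003 |

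The formula gives −0.6 × 0.25 = −0.150 for the −0.146 cell. Over shifts of 0.1 to 0.5 SD and b of 0.2 or 0.4, the adjusted term ran from −0.005 to 0.009 without a common cause and from −0.250 to −0.049 with one.

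**6. Same-direction case.** With s = 0.3 in both sexes, b = 0.4 and g = 0.5, the mobility-by-sex term loses nothing. The mobility effect within each sex, truly 0.3 × 0.4 = 0.12, would become −0.3 × 0.25 = −0.075 with stress held fixed. The problem of reading effects at a given stress level therefore does not depend on opposite shifts; the damage to the sex term does.

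**The case against.** Several points on the other side are sound.

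- **The sex term is not shown to be harmed.** A reader might infer that part of the sex effect will be conditioned away. The article does not support that. Stress appears only in a parenthesis in the aim; H2, the aims overview and Fig. 2 use sex alone. The loss arises only if stress is fitted with sex or results are stratified by stress, and no such model is described.
- **Stress did not move oppositely on every measure.** School-performance and school/leisure stress rose in both sexes. If that is the stress intended, the effect on the sex term could be small.
- **No size can be claimed.** A reader might take 0.08 to 0.24 SD as the expected loss. Those figures need invented, equal and opposite shifts, and the simulation makes the same assumption of opposite shifts.
- **A variable can be both mediator and modifier.** Exposure-by-mediator interaction is a legitimate estimand, and Aim 2 speaks of links rather than causal subgroup effects.
- **The stress pathway may be analysed elsewhere.** Its absence from Aim 3 does not show that it will never be estimated, because the full analysis plan is not shown.

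These limit the consequence but leave the core. The article assigns stress a moderator role in one place and a causal-pathway role in another, does not limit it to a pre-lottery measure, and rests its causal claims on a lottery that does not protect comparisons within post-lottery stress levels.

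**Conclusion.** The concern holds in a limited form. As Aim 2 is worded, adolescent stress is a moderator that the article itself reports as changed by the lottery and describes as a cause of the outcome. Unless the measure predates the lottery, mobility effects within stress levels, and the mobility-by-stress term, have no causal reading.

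H2 tested by sex alone is unaffected. If stress is fitted jointly with sex, the mobility-by-sex term excludes whatever passes through stress, by (s_F − s_M) × b. That amount cannot be computed from the article and ranges from nothing, if the sexes shifted alike, to the whole of a stress-transmitted difference.

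The conclusion assumes that the moderator is a post-lottery measure, which is the likelier reading but is not stated, and that the stress findings in section 1.3 apply to this cohort. The point should be corrected before analysis; it does not undermine the study as a whole.

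**What to change.** Reword Aim 2 and fix the models accordingly:

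1. Keep sex as the Aim 2 moderator and test mobility-by-sex in a model without post-lottery stress.
2. Use stress as a moderator only if it was measured before the lottery, and name the instrument and wave.
3. Analyse post-lottery adolescent stress from the earlier waves as a mediator (mobility to stress to inflammation and microbiome), with the first path moderated by sex. State the assumption of no unmeasured confounding between stress and outcome, which the lottery does not secure.
4. Label any stress-stratified or mobility-by-stress result as descriptive.

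The cost is a change of wording and one further model. No new data collection appears necessary: section 1.3 already reports stress during adolescence, and section 3.2.1 says assessments from earlier waves will supplement the extension. The drawback is that the mediated path rests on an assumption that cannot be verified.
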